#### Process evaluation outcomes

With the aim of evaluating the implementation process a qualitative survey will be performed. For conducting qualitative interviews with patients and employees during the intervention phase a semi-structured interview guide will be developed. Five of the indicators proposed by Proctor et al. [17] [17] will be the focus in the interviews and evaluation process acceptability, adoption, appropriateness, feasibility and fidelity. Moreover, to explore the patient-centeredness of the intervention, access to care and clinician-patient relationship will be investigated [18]. Finally satisfaction with treatment will be explored. Interviews will be conducted by scientific staff.

#### Economic evaluation outcomes

Primary economic outcomes are inpatient and outpatient costs, costs for medication and nursery.

### Data analysis

#### Analysis of effectiveness outcomes

The structural equality of the control and intervention groups at baseline will be examined to detect imbalances, using descriptive statistical analysis.

In order to evaluate the intervention effect on the two primary outcomes at the 12-months follow-up, data will be analyzed using linear mixed models. In the fixed part of the model, exposure to the intervention (StroCare vs usual care) will be included as the independent variable of interest. Potential confounding variables will be added as fixed effects in case of baseline imbalance, including demographic characteristics, stroke type and severity of stroke symptoms, as well as vascular and systemic features. The random effects part of the model will include variance parameters for the intercept and for the treatment effect across the participating clinics, respectively. Findings regarding the primary outcomes with an alpha error rate below 0.025 will be considered statistically significant (Bonferroni adjustment for two outcomes).

The primary outcome at the 24-months follow-up and the secondary outcomes will be analyzed using similarly structured models. In the case that data are not normally distributed, generalized mixed models will be applied. Findings regarding the secondary outcomes with an alpha error rate below 0.05 will be considered statistically significant.

Parameter estimates will be reported with 95% confidence intervals. Missing values will be handled using multiple imputation.

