### Study description and study design

The StroCare intervention will be evaluated in a multi-center mixed-methods sequentially controlled intervention study with a longitudinal design (Fig. 1). Onset is acute inpatient stroke treatment with subsequent neurological rehabilitation. Patients will be enrolled during their initial stay at the stroke unit for the control and intervention group during a 12 months period each, starting with the control group. Afterwards, the intervention will be deployed and enrolment in the intervention group will start. For individual patients, the intervention will cover a period of 24 months. The intervention effects on outcomes will be evaluated by a quantitative survey 12 and 24 months after stroke. In terms of the implementation process, qualitative interviews will be conducted with patients after the implementation of the interventions. Additionally, employees (doctors, nurses, and IT staff) involved in the study will be interviewed before and after the implementation of the interventions. Comparative analyses of health-care costs are planned 6 and 12 months after admission with admitted permission to insurance data files. Enrolment of patients in the control group started in January 2020. Scheduled duration of the entire study from first-patient-in to last-patient-out has been extended from 24 to 36 months due to the COVID-19 pandemic.

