### Perspective

This study combines different aspects of health care (primary contact, outpatient managed care, case management, coverage of costs by the health insurance company and an electronical allocation of capacities) in order to improve managed care of stroke patients. The study will not only provide information on the tested intervention but is likely to be helpful for stakeholders and researchers implementing and evaluating complex interventions in stroke care in general. The StroCare interventions will be established at three acute-care clinics with different care structures including five rehabilitation clinics in northern Germany and a nationwide health insurance company. Thus, the health care system will have an evaluated reference model at its disposal for transfer to other regions as well as organizational structures and processes.

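### The groups are formed by calendar phase, yet confounders enter the primary model only if baseline looks imbalanced; the plan should fix the adjustment set and state that period cannot be separated from the intervention

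*Protocol article*

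**What the plan says.** Under Study description and study design, the protocol article describes two consecutive enrolment phases of 12 months each, controls first. "Enrolment of patients in the control group started in January 2020"; of the second phase it says: "Afterwards, the intervention will be deployed and enrolment in the intervention group will start". The same section names COVID-19 only as a reason for a longer study: the duration "has been extended from 24 to 36 months due to the COVID-19 pandemic".

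Under Analysis of effectiveness outcomes, the primary analysis is a linear mixed model with group as the fixed effect of interest and, across clinics, a random intercept and a random treatment effect. On covariates: "Potential confounding variables will be added as fixed effects in case of baseline imbalance". The candidates are listed as "including demographic characteristics, stroke type and severity of stroke symptoms, as well as vascular and systemic features". Equality of the groups at baseline "will be examined to detect imbalances, using descriptive statistical analysis". No criterion for imbalance is given, and no term for calendar time appears in the fixed or the random part.

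**The concern.** In a randomised trial, an observed baseline difference is chance. Here the groups are defined by when the patient was admitted, so systematic differences are to be expected whether or not the baseline table shows them. A rule that waits for visible imbalance has three consequences.

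- The model for both primary outcomes is chosen after the data are seen, by a criterion nobody has written down.
- A real difference that happens to look small is left unadjusted.
- Prognostic factors such as age, stroke type and severity are left out when they look balanced, although they would sharpen the estimate.

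A second issue sits beside this one. Every control precedes every intervention patient, so anything that changes between the phases is part of the estimated StroCare effect. The article does not say so.

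**Working it through.** **Inputs from the article (Sample size calculation).** d=0.3; alpha 0.025 per primary outcome; power 80%; 213 evaluable patients per group. Sidedness is not stated; two-sided reproduces the figure.

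**Assumed inputs.** The article gives no size of imbalance, no R² and no trigger. I take one confounder with a true difference of 0.15 SD and correlation r=0.5 with PROMIS (R²=0.25), and two possible triggers: p<0.05, and an absolute standardised mean difference (SMD) above 0.1.

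**1. The plan's own figure.** n = 2(z₀.₉₈₇₅ + z₀.₈₀)²/d² = 2(2.241+0.842)²/0.09 ≈ 211.2, so 212; the t-test version gives 212.5, so 213. This matches the article and assumes no covariate adjustment. Power at 213 per group is 80.1%.

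**2. Residual bias.** The observed confounder difference D is approximately normal with mean 0.15 and SE √(2/213) = 0.0969. If flagged, the adjusted estimate is unbiased. If not flagged, the bias is r·D. With cut-off c, a=(−c−0.15)/0.0969 and b=(c−0.15)/0.0969:

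residual bias = r × {0.15·[Φ(b)−Φ(a)] − 0.0969·[φ(b)−φ(a)]}

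- p<0.05: c=1.96×0.0969=0.190, a=−3.51, b=0.412. Not flagged 66%, flagged 34%. Bias = 0.5 × (0.0989 − 0.0354) ≈ 0.032 SD, about 11% of d=0.3.
- SMD>0.1: c=0.1, a=−2.58, b=−0.516. Not flagged 30%, flagged 70%. Bias = 0.5 × (0.0447 − 0.0325) ≈ 0.006 SD, about 2% of d=0.3.
- Never adjusted: 0.5×0.15 = 0.075 SD. Always adjusted: 0.

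Simulation agrees (0.032, 0.006, 0.074 and about 0). For true imbalances of 0.10 to 0.20 SD and R² of 0.1 to 0.5, the range is 0.017 to 0.045 SD under p<0.05 and 0.001 to 0.011 SD under SMD>0.1.

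**3. Power with truly balanced groups, d=0.3, 213 per group.** Always adjusting: two-sample t-test power at d/√(1−R²). For R²=0.25, 0.3/√0.75 = 0.346. The conditional rules were simulated.

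| R² | p<0.05 trigger | SMD>0.1 trigger | always adjusted |
|---|---|---|---|
| 0.10 | 81% | 82% | 84% |
| 0.25 | 81% | 85% | 91% |

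With balanced groups the p<0.05 trigger fires about 5% of the time and the SMD trigger about 30%, so most of the possible gain is lost under either.

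These figures leave out the random treatment effect across clinics, which patient covariates do not reduce. As an illustration, assume a between-clinic SD of the effect of 0.1 over three clinics. This adds 0.01/3 = 0.0033 to the variance: unadjusted SE = √(0.0094+0.0033) = 0.113, power about 66%; at R²=0.25, SE = √(0.0070+0.0033) = 0.102, power about 76%. The gain remains, at a lower level.

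**4. Period.** Group and phase coincide, so a between-phase shift δ adds fully to the estimate. With no true effect, rejection = P(|Z + δ/0.0969| > 2.241): 11% at δ=0.1 SD and 43% at 0.2 SD, against 2.5%. A shift of 0.1 SD against StroCare lowers power from 80% to 43%. The values of δ are assumed, and covariate adjustment for patient characteristics does not remove such a shift.

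**The case against.** The article names the classes of candidate confounders in advance, so the model is not wholly post hoc, and an analysis plan not shown may list exact variables and a threshold. That stands in part. But the article does more than leave detail open: it states the conditional rule, and a threshold would complete that rule without changing its kind.

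The bias may also be small. The article mentions no significance test; under an SMD trigger of 0.1 the residual is about 0.006 SD for one confounder. Nor does the rule inflate false positives much in this setting: in the simulation of the 0.15 SD case, rejection with no true effect was about 2.8% under p<0.05 and 2.3% under SMD>0.1. This stands. Several confounders screened separately could leave more.

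Stronger readings that a reader might infer, and that the documents do not support:

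- That the plan carries a 0.075 SD bias (25% of d=0.3), or that adjustment lifts power from 80% to 91%. Both compare with never adjusting, which is not the stated rule. No baseline PROMIS-10 is described, so R² may be nearer 0.1.
- That the period bias is avoidable. With non-overlapping phases, no covariate separates period from treatment without extrapolation.
- That the pandemic is known to have moved PROMIS scores. Nothing in the article shows this; the shifts above are assumptions.
- That the insurer could supply a concurrent comparison. Calling it "a nationwide health insurance company" does not establish access to data on patients at other hospitals, and claims data would not address PROMIS.

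**Conclusion.** The concern holds in a limited form. Conditional adjustment, judged descriptively and without a threshold, is the wrong kind of rule for a comparison of consecutive cohorts, and it governs both primary outcomes. Under the stated assumptions it leaves about 0.006 to 0.03 SD of bias for one confounder with a 0.15 SD difference. With balanced groups it gives about 81% to 85% power, where always adjusting gives 91% (R²=0.25); at R²=0.1 the comparison is 81% to 82% against 84%. The size is modest and depends on the trigger. The remedy costs so little that it should be made before any group comparison is seen.

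Separately, the intervention effect is fully aliased with calendar period. That belongs in the plan as a stated limitation; covariate choice cannot correct it.

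**What to change.** 1. Replace the conditional sentence under Analysis of effectiveness outcomes with a fixed adjustment set, included whatever the observed balance: age, sex, stroke type, severity of stroke symptoms, main vascular comorbidities, and premorbid mRS if its value is recorded (the eligibility criteria use it only as an exclusion threshold). Keep clinic in the random part, where it already is. Keep the baseline table as description only.
2. State that the effect estimate cannot be separated from calendar period, including the pandemic, because all controls precede all intervention patients. Soften attribution to match, including the Perspective section's claim to supply an evaluated model for transfer elsewhere.
3. Optionally, prespecify a model with a within-phase time trend as a sensitivity analysis only. It relies on extrapolation between the phases and is less precise than the primary model.

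**Cost.** Items 1 and 2 are wording. The covariates are factors the article already names as candidates or collects, apart from the condition on premorbid mRS. Item 3 is one extra model. No patients or visits are added.

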### Sample size calculation

In order to assess the effectiveness of the StroCare intervention, the two prospective groups will include all patients insured with the health insurance BARMER who will be hospitalised in one of the three participating clinics over a period of 24 months for stroke treatment and have given their written consent. Previous studies showed moderate to large effects of similar interventions on health-related quality of life with standardized mean differences (Cohen’s *d*) between treatment and control groups ranging from 0.2 to 0.6 [8, 12]. We aim to identify a moderate effect (Cohen’s *d*=0.3) of the intervention on patient’s experienced health-related quality of life. With a power of 80% and an alpha error of 0.025 (adjusted for two primary endpoints, the two subscales of the PROMIS-10), a sample size of *N*=213 patients per group (426 in total) will be needed. Accounting for an expected dropout rate of 10% results in a necessary sample size of 235 per group (470 in total). In the past few years, approximately 600 patients insured with BARMER with a diagnosis of stroke were treated annually in the three participating clinics. In the planned time frame of 24 months we thus expect to enroll the planned number of 426 patients if 39% of 1200 participants participate.

For the qualitative interviews it is indicated that on average 12 interviews are sufficient to reach theoretical saturation [13]. Thus, the planned sample size of a maximum of 21 patients enrolled in the intervention group and 20 employees of different departments (doctors, nurses, and IT staff) represents a meaningful basis for the investigation of the experience gained during the implementation.

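### The sample size assumes a plain two-group comparison, but the primary model adds a random treatment effect across only three clinics, so 80% power and 2.5% error are not delivered together

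*Protocol article*

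**What the plan says.** The section on analysis of effectiveness outcomes specifies linear mixed models for the two PROMIS-10 scales at 12 months. Intervention exposure is the fixed effect of interest, and "The random effects part of the model will include variance parameters for the intercept and for the treatment effect across the participating clinics, respectively". The test level is 0.025 per outcome: "Findings regarding the primary outcomes with an alpha error rate below 0.025 will be considered statistically significant (Bonferroni adjustment for two outcomes". The 24-month and secondary outcomes are to use models of similar structure.

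The sample size section works from a standardised difference ("We aim to identify a moderate effect (Cohen’s *d*=0.3"), "With a power of 80% and an alpha error of 0.025 (adjusted for two primary endpoints, the two subscales of the PROMIS-10", and concludes that "213 patients per group (426 in total) will be needed". Dropout is then added: "Accounting for an expected dropout rate of 10% results in a necessary sample size of 235 per group (470 in total". No other input is named.

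The number of clinics is three: patients are those "hospitalised in one of the three participating clinics over a period of 24 months". The aim and perspective sections give the same count of acute hospitals. The five rehabilitation centres do not add levels, because patients are enrolled on the stroke unit of an acute hospital.

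**The concern.** A random treatment effect means that the average effect is judged against how much the effect differs between clinics. With three clinics that difference rests on 2 degrees of freedom, so its variance is often estimated as zero and otherwise is very noisy. The sample size makes no allowance for this. The two sections therefore describe different analyses: one sets the power, the other is carried out.

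At stake is the confirmatory test of both primary outcomes. A real effect of the planned size would be missed more often than the stated 20%. If the effect differs between clinics, the false-positive rate may also move away from 2.5%.

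**Working it through.** **Inputs from the article.** d = 0.3 (SD 1 on the standardised scale), power 80%, alpha 0.025 per outcome, 213 evaluable per group, three clinics, random intercept and random treatment effect by clinic.

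**Assumptions.** Equal clinics, so 213/3 = 71 patients per arm per clinic; two-sided testing, which is what reproduces the stated number (one-sided gives 175); no covariates. The SD of the treatment effect across clinics (τ, in outcome-SD units) is not in the article; the range 0 to 0.3 is assumed.

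**Step 1: the plan's own figure.** n = 2(z₀.₉₈₇₅ + z₀.₈₀)²/d² = 2(2.241 + 0.842)²/0.09 = 211.2, so 212 by the normal approximation. The t-test version gives 212.5, so 213. The stated figure is reproduced, and it contains no clinic term.

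**Step 2: the common-effect benchmark.** Each within-clinic difference has sampling variance v = 2/71 = 0.0282. The mean of three has standard error √(0.0282/3) = 0.0969. Then 0.3/0.0969 = 3.096, and power = Φ(3.096 − 2.241) = Φ(0.855) ≈ 80%.

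**Step 3: the planned model.** The clinic differences have variance τ² + v. With S² their sample variance, the REML estimate of τ² is max(S² − v, 0), and the ML estimate is max(2S²/3 − v, 0). The standard error is √((estimate + v)/3).

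- *How often the REML estimate is zero.* 2S²/(τ² + v) is chi-squared on 2 df, so P(S² < v) = 1 − exp(−v/(τ² + v)). At τ = 0 this is 1 − e⁻¹ = 63%. At τ = 0.2 it is 1 − exp(−0.0282/0.0682) = 34%.
- *Why power falls even at τ = 0.* With equal clinics the point estimate is the same as in step 2, and the standard error is never smaller. In the 37% of trials with a positive variance estimate it is larger. The Wald test therefore rejects less often than the 80% benchmark.
- *Clinic-level test on 2 df.* The critical value is 6.205 instead of 2.241. The noncentrality is 0.3/√((τ² + v)/3), which is 3.096 at τ = 0.

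Results (simulation of the three clinic differences, 1,000,000 trials per setting; noncentral t for the 2-df test):

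| τ | Power, REML Wald | Power, ML Wald | Type I error, REML Wald | Power, 2-df clinic-level test |
|---|---|---|---|---|
| 0 | 70% | 76% | 1.8% | 23% |
| 0.1 | 62% | 69% | 3.5% | 18% |
| 0.2 | 47% | 56% | 7.5% | 12% |
| 0.3 | 36% | 44% | 10.9% | 8% |

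The 2-df test holds 2.5% error throughout. The REML Wald error crosses 2.5% at τ between 0.05 and 0.1. With unequal clinics (assumed 120, 60 and 33 per arm), REML Wald power runs from 68% to 36% and error from 1.8% to 12.0% over the same range of τ.

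**Step 4: the alternative on the same footing.** With clinic as a fixed effect and one treatment effect, 213 per group gives about 80% power at 2.5% error when τ = 0. If the result is read as applying to a wider population of clinics, its type I error is 5.4%, 15.0% and 27.4% at τ = 0.1, 0.2 and 0.3, which is worse than the planned model.

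**The case against.** Four points can be made for the plan.

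*A random treatment effect suits the stated purpose.* The perspective section wants a reference model that can be transferred to other regions, from clinics that differ in structure. Letting the effect vary by clinic is a reasonable choice for that aim, and the fixed-clinic model is worse by that yardstick (step 4). This stands as a real cost of the fix. It does not make three clinics enough to estimate the variance.

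*The estimation method, degrees of freedom and handling of singular fits may be in an SAP that is not shown.* Agreed, and their absence is not criticised here. But none of the conventions tried gives 80% power while the random treatment effect is kept. The difficulty lies in the stated model.

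*A reader might infer that the primary test has almost no power.* That goes too far. The 23% belongs to a t-test on three clinic-level differences, which the article does not specify. A rough rule that uses residual degrees of freedom when the variance estimate is zero, and 2 otherwise, gives about 51% at τ = 0. Wald tests give 70% to 76%.

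*A reader might also infer that the type I error must exceed 2.5%.* The documents do not support that. The Wald test is conservative at τ = 0, and the 2-df test holds its level. Inflation needs both a Wald-type or data-driven reference distribution and a τ above roughly 0.05 to 0.1, and the article gives no value of τ.

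**Conclusion.** The point holds in a limited form. The sample size section and the primary model do not match, and the stated model does not give 80% power and 2.5% error together. The power shortfall needs no assumption about heterogeneity: about 4 points (ML) to 10 points (REML) are lost with a Wald test even when the effect is identical in all clinics, and more otherwise. The error-rate part is conditional on τ and on the reference distribution. The exact sizes rest on equal clinics, no covariates and the assumed range of τ; the assumed unequal split changes them little.

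**What to change.** In the section on analysis of effectiveness outcomes, replace both random terms by clinic as a fixed effect (two indicators) with a single treatment effect. Report clinic-specific effects and the treatment-by-clinic interaction descriptively. This is the analysis that the 213 per group supports: about 80% power at 2.5% error when the effect does not differ between clinics. Carry the change through to the 24-month and secondary models, and make it before outcome data are analysed.

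It needs wording only, with no new patients or data, but it changes what the primary analysis estimates. The article should say that the primary inference applies to these three clinics and that the primary test does not support transfer to other regions.

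If the random treatment effect is kept, restate the power in the sample size section as below 80%, with the assumed τ and the reference distribution. Adding patients is not a practical way out for the 2-df test: 80% power needs a noncentrality of 8.01 even at τ = 0, which is 2 × (8.01/0.3)² ≈ 1,426 per group.

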### Outcome measures

#### Effectiveness

In order to assess the effect of intervention, patient-reported outcomes will be surveyed measuring health-related quality of life (Fig. 3). They will be measured 12, and 24 months after baseline, using the questionnaire “Patient Reported Outcome Information System 10-Question Short Form” (PROMIS-10). The PROMIS-10 is a standardized questionnaire and consists of two scales measuring mental health and physical health [14], respectively, which will serve as the two primary outcomes. For evaluation of the PROMIS-10, at first a sum score and afterwards a t-score with standardized t-values is calculated. Reference of M ± SD= 50 ± 10 regards to a sample of healthy American subjects.

Additionally, the secondary outcome of depression and anxiety symptoms will be measured at all time points, using the “Patient Health Questionnaire-4” (PHQ-4) [15]. This questionnaire entails the two dimensions, depressive and anxiety symptoms, with two items each. The sum score ranges from 0 to 6 in each dimension. A score of 3 or higher indicates a potential anxiety or depression. The patient’s functional status will be assessed by the modified Rankin Scale questionnaire (smRSq) [16]. The scale of the smRSq ranges from 0 (“no symptoms”) to 6 (“death”). The outcomes of overall survival and stroke recurrence will be measured with the ICHOM-Standard set for Stroke [11]. The ICHOM-Standard Set for Stroke was developed under the coordination of the International Consortium for Health Outcomes Measurements (ICHOM) and measures a range of patient-reported outcomes from functionality to general health status. Further secondary outcomes are: utilization of health care services, patient’s waiting time between treatment phases, success in regaining target values of relevant risk factors (blood pressure, LDL-cholesterol, HbA1c) and costs. These parameters will be measured via the medical patient record and the rehabilitation portal. Also, a sociodemographic questionnaire will be used, measuring age, gender, living situation, partnership, vascular and non-vascular comorbidities.

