#### Analysis of the economic outcomes

We will employ both two-part (binomial, gamma) and generalized linear models (gamma distributed outcome) to analyze health care costs, because these models can incorporate the special features of cost distributions – i.e. right skewed distributions that contain a large proportion of zero values [20]. Cox-regression or frailty models as well as generalized linear models will be considered to analyze secondary outcomes such as rehospitalizations, the duration of hospital stays or the utilization of specific services.

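### Overall survival and stroke recurrence are sent to mixed models with blanket imputation, with no provision for censoring or for death as a competing event

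*Protocol article*

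**What the plan says.** Under Outcome measures, Effectiveness, the protocol article states: "The outcomes of overall survival and stroke recurrence will be measured with the ICHOM-Standard set for Stroke". The list that follows opens with "Further secondary outcomes are: utilization of health care services, patient’s waiting time between treatment phases", which places the two outcomes among the secondary ones. The section does not say whether they are event times or status at a fixed time. The study design section says: "The intervention effects on outcomes will be evaluated by a quantitative survey 12 and 24 months after stroke".

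Under Analysis of effectiveness outcomes, the primary outcomes get a linear mixed model with a random intercept and a random treatment effect across clinics. The section continues: "The primary outcome at the 24-months follow-up and the secondary outcomes will be analyzed using similarly structured models". It adds "In the case that data are not normally distributed, generalized mixed models will be applied" and closes with "Missing values will be handled using multiple imputation". No outcome is exempted from either rule.

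Event-time methods appear once, under Analysis of the economic outcomes: "Cox-regression or frailty models as well as generalized linear models will be considered to analyze secondary outcomes such as rehospitalizations". The other examples given there are length of hospital stay and use of services. Survival and recurrence are not named.

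**The concern.** A method is stated for these two outcomes, so this is not simply detail left to an analysis plan that is not shown. The method has no place for a patient who is followed for part of the period and then lost.

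- **Survival.** If deaths are learned of while a patient is still followed, an early death gives a known final status, but a patient who leaves early and alive gives none. Patients with known status are then enriched for deaths, more so where drop-out is higher, even if drop-out has nothing to do with health. Analysing or imputing final status from those patients carries this into the group comparison.
- **Recurrence.** A patient who dies without a recurrence cannot have one later. Read literally, a blanket imputation rule could fill in a later recurrence status for that patient.

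Unequal loss is plausible here. The intervention group is telephoned every three months and seen every six for two years. The control group has usual care, with no study contact described after enrolment beyond the outcome surveys. Both outcomes are tested at 0.05.

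**Working it through.** **1. The plan's own figures.** No figure is given for survival or recurrence. The inputs taken from the sample size section are 235 patients per group and one expected drop-out rate of 10%, not split by group. The calculation behind them reproduces: a two-sided t-test with d = 0.3, alpha 0.025 and power 80% needs 212.5, so 213 per group, and 213 × 1.10 = 234.3, so 235.

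**2. Assumptions.** The document gives neither mortality nor drop-out by group. Assumed: true 24-month mortality p, the same in both groups; exponential death times; independent exponential drop-out reaching d by 24 months; every death before drop-out is seen; status after drop-out is never learned.

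**3. Formula.** Let a = −ln(1 − p) and c = −ln(1 − d).
- Seen to die: D = a/(a + c) × [1 − (1 − p)(1 − d)]
- Seen alive at 24 months: A = (1 − p)(1 − d)
- Mortality among those with known status: D/(D + A)

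Imputing within group without follow-up time has the same expectation.

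Example with p = 0.20:
- d = 0.30: a = 0.2231, c = 0.3567, D = 0.3849 × 0.44 = 0.1693, A = 0.56, giving 0.1693/0.7293 = 23.2%.
- d = 0.10: c = 0.1054, D = 0.6793 × 0.28 = 0.1902, A = 0.72, giving 0.1902/0.9102 = 20.9%.
- The spurious difference is 2.3 percentage points, although true mortality is 20% in both groups.

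**4. Range, and effect on the test.** The error rates come from 2,000 simulated trials of 235 per group, with 20 imputations drawn within group and no true difference. They are compared with a log-rank test censored at drop-out. The simulation standard error near 5% is √(0.05 × 0.95/2000) = 0.5 points. Clinic effects and covariates are left out.

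| True mortality | Drop-out, control vs StroCare | Known-status mortality | Difference (points) | Type I error, imputed status | Type I error, log-rank |
|---|---|---|---|---|---|
| 10% | 10% vs 10% | 10.50% vs 10.50% | 0 | 5.50% | 5.45% |
| 10% | 15% vs 5% | 10.78% vs 10.24% | 0.54 | 4.95% | 4.40% |
| 10% | 30% vs 10% | 11.81% vs 10.50% | 1.31 | 6.45% | 4.80% |
| 10% | 40% vs 10% | 12.71% vs 10.50% | 2.22 | 9.70% | 4.65% |
| 20% | 10% vs 10% | 20.90% vs 20.90% | 0 | 4.75% | 4.95% |
| 20% | 15% vs 5% | 21.40% vs 20.43% | 0.97 | 5.55% | 5.20% |
| 20% | 30% vs 10% | 23.22% vs 20.90% | 2.32 | 9.20% | 5.35% |
| 20% | 40% vs 10% | 24.78% vs 20.90% | 3.88 | 13.35% | 4.00% |

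For scale, at 15% mortality and 235 per group the standard error of the difference is √(2 × 0.15 × 0.85/235) = 3.3 points.

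**5. Direction.** The table assumes that deaths are seen up to drop-out. Two other forms of loss give different answers:
- If loss is non-response at the survey, unrelated to vital status, mortality among responders is still p and the bias is zero.
- If a share u of deaths shows up only as non-response while all survivors respond, observed mortality is p(1 − u)/(1 − pu), which is below p. Where this happens mainly among controls, the error runs against StroCare.

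**6. Recurrence.** Suppose a share m dies without regard to recurrence, and a share r has a recurrence. If status is imputed for those who died without one, the invented recurrences amount to m(1 − r)r, or m(1 − r) relative to the real ones. With assumed m of 5% to 15% and r of 5% to 10%, this runs from 0.05 × 0.90 = 4.5% to 0.15 × 0.95 = 14.3%. It applies only if the imputation is in fact carried past death.

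**The case against.** The strongest reply is that nothing in the article makes these outcomes event times. They are surveyed at 12 and 24 months. Status at a fixed time is a legitimate target, and a logistic mixed model, which the plan allows for non-normal data, is a valid analysis of it when status is known for nearly everyone. All patients belong to one insurer, which gives access to patient data, so vital status might be complete even where the survey is not. The functional scale scores death as 6, so death is a recorded state there. The imputation model is detail that an article may leave out, and the stated drop-out is a single 10%.

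Much of this stands. It rules out the reading that mixed models are wrong for these outcomes in every case, and it makes the bias conditional. Three things remain:
- The text does not tie insurer data to survival or recurrence.
- The imputation sentence has no exception, and death is not addressed as a competing event for recurrence.
- Cox and frailty models are only to be considered, in another section and for other named outcomes.

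A reader might also infer that unequal drop-out will produce a false survival gain for StroCare. The documents do not support that. They give no drop-out by group, and the sign changes with the way deaths among lost patients come to light. Nor do they say that recurrence will be imputed after death; that follows only from a literal reading of one general sentence.

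**Conclusion.** The point holds in a limited, conditional form. The plan assigns overall survival and stroke recurrence to a method that cannot use partial follow-up, although methods that can are already named elsewhere in the same article.

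Under the stated assumptions (equal true mortality of 10% to 20%, deaths seen until drop-out, imputation that ignores follow-up time), the spurious difference is zero at equal drop-out. It is at most about 1 point at 15% vs 5%, with the type I error essentially unchanged, and 1.3 to 2.3 points at 30% vs 10%, with a type I error of about 6.5% to 9.2%. A censored log-rank test stays at about 4% to 5.5% throughout. Near the planned 10% drop-out the practical effect is therefore small; it matters only if loss is both large and unequal.

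The recurrence problem does not need unequal loss, but it does depend on imputation running past death. The PROMIS-10 primary outcomes are not touched by this point.

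**What to change.** State in the analysis section that:
- overall survival is analysed as time from the index event, with Kaplan-Meier curves and a Cox model stratified by clinic (or with a clinic frailty), adjusted for the same confounders as the primary model and censored at last known vital status;
- time to first recurrence is analysed with a cause-specific Cox model and cumulative incidence curves, with death as the competing event;
- both outcomes are excluded from multiple imputation.

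The cost is a change of wording in the analysis plan, plus the recording of event dates and the date of last known status beside the yes/no answers. No change to sample size or visit schedule is needed. The gain is confined to secondary outcomes and will be small if follow-up proves nearly complete and balanced.
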